## Methods and analysis

### Patient and public involvement

Patient partners who have recovered from sepsis will be recruited from the ICU Follow-Up Clinic at Kingston Health Sciences Centre (Kingston, Ontario). Patient partners will help to guide decision-making around the clinical outcomes that are most important to study, such that our analysis can be focused on patient-centred outcomes.

### Study design and setting

To expand our understanding of FES involvement in mediating sepsis, we will perform *in vitro* and *in vivo* modeling to elucidate the degree of inflammatory signaling, cytokine production, and NET formation that occurs in wild-type (WT) and *FES* knockout (*FES^-/-^
*) mice. Using clinically available treatments that either enhance *FES* expression or inhibit FES activity, we will explore the utility of early *vs.* late FES modulation on outcomes in WT mice. Finally, we will explore the clinical relevance of FES in the pathogenesis of sepsis by using bioinformatic analyses to examine *FES* expression levels in RNA transcriptomic data from publicly available cohorts of patients with sepsis and healthy controls and correlating this with clinical outcomes. All analyses will take place in the Queen’s Cancer Research Institute facility at Queen’s University (for experimental laboratory-based aims), or the Centre for Advanced Computing (for the clinical bioinformatics aims).

### 
*In vitro* methodology

Bone marrow derived macrophages (BMDMs) (26) or neutrophils (27) isolated from WT or *FES^-/-^
* mice will be stimulated with infectious surrogates (LPS or PolyI:C), or a surrogate for tissue damage-mediated sepsis (High Mobility Group Box 1; HMGB1). The degree of inflammatory signaling (e.g., NF-κB and IRF-3 phosphorylation) will be assessed via immunoblot analysis. Supernatants will be analyzed by cytokine multiplex (28) methods to determine differential cytokine production in WT or *FES^-/-^
* immune cells, and the type of cytokines (e.g., proinflammatory, such as IL-1, IL-6, IL-12, TNF-α, and Interferon-α/β (23); or anti-inflammatory, such as, IL-10 and TGF-β (29)) (**Figure 3A**). Finally, WT and *FES^-/-^
* neutrophils will be evaluated for their ability to produce NETs using flow cytometry (30) (**Figure 3B**).

**Figure 3 f3:**
[figure not shown]
Graphical depiction of *in vitro* methodology. **(A)** Wildtype (WT) or FES^-/-^ bone marrow derived macrophages will be stimulated with LPS or other stimulating agents and analyzed for differential signaling cascade activation (immunoblot analysis) and cytokine production (enzyme-linked immunosorbent assay (ELISA)). **(B)** WT or FES^-/-^ neutrophils isolated from the spleen will be stimulated with LPS or other stimulating agents and analyzed for differential signaling cascade activation (immunoblot analysis), cytokine production (ELISA), and neutrophil extracellular trap formation (flow cytometry). The same methodology will be followed with the addition of decitabine and lorlatinib. Created with BioRender.com.

BMDMs and neutrophils isolated from WT or *FES^-/-^
* mice will be pre-treated with either a drug that inhibits FES activity (*lorlatinib* (31)), or one that increases *FES* transcription (*decitabine* (32)). These cells will then be stimulated with LPS, PolyI:C, or HMGB1 to simulate the immune cell activation associated with sepsis, and the same methodology as in Aim 1 will be used to assess increased (in the case of lorlatinib treatment) or decreased (in the case of decitabine treatment) hyper-inflammatory signaling, cytokine production, and NET production.

### 
*In vivo* methodology

WT or *FES^-/-^
* mice will be treated in one of two ways, either simulating different insults resulting in sepsis: 1) cecal ligation and puncture (CLP), the gold-standard sepsis model (33) or 2) a cecal slurry (CS) of 0.5mL of a solution at a fecal concentration of 45mg/mL (33–35). Following induction of sepsis, mice will be closely monitored and scored on the murine sepsis score (MSS), which assesses sepsis severity based on appearance, level of consciousness, activity, response to stimulus, eyes, respiration rate, and respiration quality (35). The MSS has been shown to have a specificity of 57%, and a sensitivity of 100% for predicting onset of severe sepsis and death following CS. Blood will be collected by cardiac puncture at the 24h time point and analyzed by cytokine multiplex to assess differential cytokine production, which will demonstrate differences in cytokine production from either WT or *FES^-/-^
* genotypes and can also be correlated with sepsis severity (35). Additionally, the following biomarkers will be assayed from the blood, as these have been associated with sepsis in murine models: C-reactive protein (CRP), soluble triggering receptor expressed on myeloid cells-1 (sTERM-1), CD163, procalcitonin (PCT) and hypoxia-inducible factor (HIF-1α) by ELISA, where CD163 and procalcitonin can stratify mice further into a state of severe sepsis (36) (**Figure 4**). Spleens will be isolated, dissociated and analyzed by flow cytometry for the presence and activation of immune cells (i.e., macrophages, neutrophils, T cells, B cells), as well as NET formation (30). Finally, differences in clotting ability and end-organ damage between WT and *FES^-/-^
* mice will be assessed by histopathological analysis of hematoxylin & eosin-stained necropsy tissues. Briefly, livers, kidneys, small intestines, lungs, and brains will be assessed for necrosis, edema, accumulation of immune cells within tissues (e.g. macrophages, neutrophils, T-cells) and signs of damage to the tissues (e.g., loss of goblet cells and villi in small intestines, debris, and loss of organization and structure of epithelium) (35). As CS with a fecal concentration of 45mg/mL is associated with a 40% survival in C57BL/6 wildtype mice, mice will be assessed for neurocognitive impairments: a significant sequalae of post-sepsis syndrome (37, 38) A recent systematic review listed several common forms of cognitive impairment found in pre-clinical models of sepsis (e.g., aversive memory, learning, locomotor and exploratory activities, short-term and long-term memories), which may mimic what happens in patient populations (37). Therefore, any surviving mice will be subjected to the Y-maze novel arm preference test (a measure of testing spatial memory and attention), buried food test (a measure of attention and organized thinking), attentional set-shifting task (a measure of attention and cognitive flexibility), and finally the open field test (a measure of motor performance) (39) (**Figure 4**). Following neurocognitive assessments, mice will be euthanized and assessed for hyper-inflammation, coagulation, and histopathology as described above.

**Figure 4 f4:**
[figure not shown]
Graphical depiction of *in vivo* methodology. Wildtype (WT) or FES^-/-^ mice will be undergo a cecal ligation and puncture (CLP) or receive a cecal slurry injected intraperitoneally. 24 hours later, mice will be assessed for the following: neurologic function assessment, serum cytokine and biomarker analysis, immunohistochemistry, and spleen immune profiling. The same methodology will be used with the addition of decitabine or lorlatinib. Created with BioRender.com.

To determine the effect of the timing of FES regulation on outcomes, WT or *FES^-/-^
* mice will be subjected to either CLP or CS and treated with lorlatinib or decitabine at either 1h (mimicking regulation in early-stage sepsis) or 12h (mimicking regulation in late-stage sepsis). Hyper-inflammation, coagulation, histopathology, and neurocognition will be assessed at 24h, as previously mentioned. Finally, to determine differential susceptibility of WT mice to sepsis, we will perform an LD_50_ analysis of both early- and late-stage treatment regimens with either drug.

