## Introduction

Sepsis is the leading cause of death among hospitalized patients in North America, and is present in over 50% of adult hospitalizations resulting in death or discharge to hospice care (1). Globally, sepsis accounts for 19.7% of all deaths (2), and is the most expensive healthcare problem requiring in-hospital treatment (3), costing the healthcare system approximately $1 billion per year in Ontario alone ($670 million for severe cases, $420 million for non-severe cases) (4). Importantly, the consequences of sepsis extend beyond the duration of the patient’s hospitalization, with lasting impairments being increasingly recognized as comprising “post-sepsis syndrome” (5); resulting in additional costs to the healthcare system for auxiliary care after discharge. Targeted treatments for sepsis are therefore urgently needed to simultaneously improve patient outcomes and alleviate the burden of sepsis on global healthcare systems.

Sepsis is characterized by widespread inflammation and life-threatening organ dysfunction, resulting from dysregulation of the patient’s response to infection and coagulation cascades (6, 7). Specifically, sepsis occurs upon disruption of the tightly regulated balance of pro- and anti-inflammatory mediators activated in response to pathogen- (e.g., virus, bacteria) or damage-associated molecular patterns (e.g., trauma; PAMPs and DAMPs, respectively) (8). Binding of PAMPs and DAMPs to toll-like receptors (TLRs) on the surface of antigen presenting cells (APCs) and monocytes causes nuclear translocation of nuclear factor kappa light chain enhancer of activated B cells (NF-κB), resulting in expression of genes encoding pro-inflammatory cytokines, tumor necrosis factor (TNF)-α, interferons, and components of complement and coagulation pathways (2). Clinically, activation of these pathways results in hypercoagulation, endothelial dysfunction, and ultimately to end organ damage (2).

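### The neurocognitive tests are justified by lasting post-sepsis impairment but set at 24h, where a group difference cannot be separated from acute sickness

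*Protocol article*

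**What the plan says.** The purpose of the behavioural tests is given in the In vivo methodology section: "mice will be assessed for neurocognitive impairments: a significant sequalae of post-sepsis syndrome". The Introduction explains the syndrome as consequences that reach past the hospital stay, "with lasting impairments being increasingly recognized as comprising" it.

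The animals are survivors: "any surviving mice will be subjected to the Y-maze novel arm preference test", followed by the buried food test, the attentional set-shifting task and the open field test. That paragraph gives no test time. It adds that the mice are euthanized after the tests and then assessed for inflammation, coagulation and histopathology.

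The time is given twice further on. The Figure 4 legend, for the general scheme, says: "24 hours later, mice will be assessed for the following: neurologic function assessment, serum cytokine and biomarker analysis, immunohistochemistry, and spleen immune profiling". The drug-timing paragraph says: "Hyper-inflammation, coagulation, histopathology, and neurocognition will be assessed at 24h, as previously mentioned". In that experiment the drugs are given at 1h for early-stage sepsis or at "12h (mimicking regulation in late-stage sepsis".

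Acute severity is scored with the murine sepsis score (MSS) on "appearance, level of consciousness, activity, response to stimulus, eyes, respiration rate, and respiration quality".

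**The concern.** The reason for the tests is a lasting sequela, but the only stated test time is one day after the insult, and the animals are not followed further. At that time a mouse may score poorly because its cognition is impaired or because it is too ill to explore, search for food or respond.

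The groups being compared are expected to differ in how ill they are. If they do, a genotype or drug effect on acute severity can appear as a neurocognitive effect even where cognition is untouched. Reading that result as evidence on post-sepsis impairment would be unsupported. It could not be repaired afterwards, because the tested mice are no longer alive.

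**Working it through.** The article has no figure to reproduce here. The check sets its statements side by side; the only arithmetic is elapsed time and a count of score items.

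**1. Purpose against time.**

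| Item | Statement | Place |
|---|---|---|
| Purpose | a sequela of post-sepsis syndrome | In vivo methodology |
| Meaning of the syndrome | lasting impairment, beyond hospitalization | Introduction |
| Test time, general scheme | 24h | Figure 4 legend |
| Test time, drug-timing experiment | 24h | In vivo methodology, drug-timing paragraph |
| Follow-up after testing | euthanasia; no later test described | In vivo methodology |

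**2. Where 24h falls on the article's own clock.** I take all times as counted from induction of sepsis.

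- Early treatment at 1h: 24 − 1 = 23h from dose to test.
- Late treatment at 12h: 24 − 12 = 12h from dose to test.

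The 12h dose stands for late-stage sepsis. The section on timing of FES regulation characterizes that stage by immune suppression and organ dysfunction. Nothing in the article describes recovery between 12h and 24h. The test time is therefore within the modelled illness, not after it.

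**3. Whether the compared groups should differ in acute severity at that time.** They should, if the study's hypotheses are right. The section on responsible cell types expects more immune activation, coagulation and organ damage in septic knockout mice than in wildtype mice. Expected impact predicts, for wildtype mice:

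| | Early treatment | Late treatment |
|---|---|---|
| Lorlatinib | more severe | less severe |
| Decitabine | less severe | more severe |

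**4. Whether acute severity can reach the test scores.** The MSS has seven items: appearance, consciousness, activity, response to stimulus, eyes, respiration rate and respiration quality. Three of the seven (consciousness, activity, response to stimulus) describe capacities that maze exploration, a food search and set-shifting require of the animal.

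**5. Together.** Genotype or drug is expected to change severity (step 3). Severity can change the test score (step 4). Both are observed on the same day with no later observation (steps 1 and 2). The article describes no way of separating the two, so a group difference at 24h has two explanations that the data cannot tell apart.

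**6. Size.** The article gives no correlation between any test and the MSS, and no expected shift in MSS. Any numerical value for the spurious difference would merely return the correlation assumed, so none is offered.

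**The case against.** The strongest reply is that this is a condensed article. The behavioural schedule may be set out in full elsewhere, and the reference to surviving mice may point to a separate cohort tested later. Blood is taken by cardiac puncture at 24h, yet euthanasia and the repeat assays come after the behavioural tests, so separate cohorts are possible. This has some force on cohort structure, which the article leaves unclear. It does not rescue the test time: the article states one, twice, and it is 24h both times. This is a stated rule that does not fit its rationale, not an omitted detail.

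A second reply is that a drug effect on behaviour through severity may be a real effect on acute brain function. That stands. It is a reason to accept 24h as an acute endpoint, but not as a measure of post-sepsis impairment.

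Several stronger readings are tempting and should not be adopted:

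- A reader might infer that lasting cognitive impairment is a formal aim. The aims sections do not mention it; it is the rationale given for these tests.
- A reader might infer that the tests would chiefly measure sickness, or duplicate the MSS. Overlap with three of seven items shows that confounding is possible, not that the measures are redundant.
- A reader might take survival as evidence of the animals' state at 24h. The statement that "CS with a fecal concentration of 45mg/mL is associated with a 40% survival in C57BL/6 wildtype mice" concerns the cecal slurry model only, has no time horizon, and does not cover cecal ligation and puncture.
- A reader might infer that the open field test is fixed as the last to be run. The word that introduces it may simply close a list.

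**Conclusion.** The concern holds as a mismatch between stated rationale and stated test time. A 24h group difference in these tests cannot be separated from acute sickness and cannot support a conclusion on post-sepsis impairment. The share of any difference that would be due to sickness is unknown.

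The conclusion rests on two assumptions: that times are counted from induction, and that no later survivor assessment exists outside the article. If the full protocol has one, the article's text still needs correcting, but the study would not have the defect.

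The point is limited to the neurocognitive readout. The severity, inflammation and coagulation results, on which the expected conclusions mainly rest, are not affected. It should be settled before the experiments start.

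**What to change.** Reconcile the neurocognition paragraph with the drug-timing paragraph and the Figure 4 legend, in one of two ways:

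- **(a) Keep 24h.** Describe the endpoint as acute neurologic function and drop the post-sepsis-syndrome interpretation. This costs only wording, but the study then says nothing about lasting impairment.
- **(b) Test designated survivors later.** Fix a day by which acute signs have resolved, and carry out the 24h terminal assays in other mice. No new test is needed. The costs are longer housing, separate mice for the 24h assays, and terminal assays in the survivors that are no longer at 24h. Survivors may also be selected differently by genotype or drug, so survival by group should be reported beside the test results.

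Under either option, state which mice contribute to which assessment and in what sequence, including the 24h cardiac puncture. Report open-field locomotion and same-day MSS beside the other three tests to help interpret them. Keep any adjustment for these two as a sensitivity analysis only: both are measured after genotype or treatment has acted, so adjusting for them can remove the effect of interest or introduce bias.

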### Clinical and bioinformatics methodology

We have previously extracted RNA from whole blood samples in critically ill patients at various time points during their admission, as well as from healthy controls, as part of the “Prevention of nosocomial infections in critically ill patients with lactoferrin (PREVAIL)” study (NCT01996579). Briefly, blood was collected into PAXgene tubes, frozen, RNA extracted, and gene expression was profiled using the Affymetrix PrimeView microarray (40). Data on 69 patients and 21 healthy controls from this analysis is publicly available (41) and will be analyzed for the current study. Machine-learning approaches will be used to identify key variables associated with FES RNA expression levels, including a) *clinical diagnosis of sepsis*; b) *illness severity*, as measured by Acute Physiology and Chronic Health Evaluation II (APACHE II) and Sequential Organ Failure Assessment (SOFA) scores; and c) clinical outcomes including *hospital length of stay and ICU mortality*.

A publicly available dataset comprised of clinical outcome data as well as SNP analysis from genome wide association studies (GWAS) will be sought through collaborations with local and international experts in the field of sepsis genetics. Multivariable analysis will be used to determine the association between the two SNPs (rs17514846 and rs1894401) related to differential FES expression, and clinical, patient-centred outcomes. Additionally, we will apply for access to the United Kingdom BioBank (https://www.ukbiobank.ac.uk/), a large-scale database with in-depth genetic and clinical outcomes for a wide variety of diseases (including sepsis) in over half a million patients. This database currently has SNP and transcriptomic data available to be paired with clinical outcomes and will soon be releasing proteomic data which can be analyzed further to pair the two SNPs (rs17514846 and rs1894401) related to differential FES expression with protein expression, and clinical outcomes.

## Expected impact

These results will determine if FES modulates sepsis severity by preventing hyper-inflammation and suppressing coagulation cascades, providing a rationale for using FES regulation as a therapeutic strategy to reduce sepsis severity. The results of these experiments will further improve our understanding of the process by which NETs are produced, which has implications not only for sepsis but also for many other diseases.

In lorlatinib treated WT immune cells, we expect to see a phenocopy of the *FES^-/-^
* immune cells, and prevention of inflammatory signaling with decitabine. Irrespective of the timing of treatment, we do not expect either lorlatinib or decitabine to affect sepsis severity in *FES^-/-^
* mice (as there is no FES present to be regulated by either of these drugs). By contrast, in WT mice we expect to see increased septic severity following early lorlatinib treatment, and decreased septic severity following early decitabine treatment. We further expect to see decreased septic severity following late lorlatinib treatment (protective effect) and increased septic severity with late decitabine treatment (detrimental effect). These findings would support the notion that FES is a critical regulator of sepsis; and would further demonstrate that sepsis severity can be attenuated using currently available treatments by differentially modulating FES depending on the stage of a patient’s illness progression.

While it is our expectation that high FES expression levels in early sepsis and low FES expression levels in late sepsis will result in improved murine and patient outcomes, it is possible that this will not be the case. However, irrespective of the direction of the association, we will capitalize on the FES expression results found in order to improve *in vitro*, *in vivo* outcomes. For example, if we find that low FES expression is associated with improved outcomes in early sepsis (contrary to our hypothesis), we will expand upon this finding by seeking to reduce FES expression in our models of early sepsis. Similarly, if–contrary to our expectations–we find that high FES expression is associated with improved outcomes in late sepsis, we will aim to increase FES expression in our models of late sepsis and evaluate changes in outcomes seen as a result of this shift in expression. Additionally, if FES expression plays no role in sepsis severity, it will allow us to rule out a potential regulator heavily involved in many aspects of sepsis, which will help to narrow in on true regulators of sepsis severity and outcomes. We expect that *FES* expression levels on microarray analysis can be used alone or in combination with other genetic features as a biomarker to determine the presence, stage, severity, and outcome of sepsis. The heterogeneity of sepsis presentation and progression has long posed a problem for determining which patients will benefit from specific therapies, and the appropriate timing of these interventions. If we find that FES expression differs between time points in the progression of septic illness (i.e., between early- *vs*. late-stage sepsis), these results may then be used in future studies to help with targeting treatments toward specific subsets of patients who may differentially benefit from therapeutic interventions applied at different time points.

Finally, we expect that two SNPs associated with differential FES expression will be useful as prognostic biomarkers to stratify patients with sepsis based on risk for adverse outcomes that are relevant to patients, with the potential predictive value to inform FES-targeted treatments based on risk.

An important note about the involvement of FES in the pathophysiology is the association of SNP rs4957796, located within an intron of the FER gene (Fps/Fes related tyrosine kinase), with reduced mortality from sepsis (42), and reduced incidence of bloodstream infections, but increased mortality in those who do develop a bloodstream infection (43). FES and FER share similar biological functions such as platelet aggregation (19), mast cell activation (13, 44) and signaling of the immunosuppressive cytokine IL-10 (13), an important signalling pathway known to limit inflammation, whose function may have differing important roles during early- (important to limit the overactivation of the immune system) and late-stage (contribution to characteristic late-stage immunosuppression) sepsis. These observations may suggest a partial explanation to the improved outcomes in patients containing the SNP, rs4957796 (42) as well as the observations surrounding bloodstream infections (43). This hints that the impact of FER and potentially FES is double-edged sword where it is crucial to have the right amount of expression at the right time to have protective effects and not exacerbate the illness. If true, this would suggest a problem that the application of precision medicine might be able to overcome.

Sepsis is a disease that is constantly under investigation to find an effective treatment because of the major consequences on human life and healthcare burden. Unfortunately, there has not been much success towards this aim; over 100 randomized clinical trials which identify a target, and directly modulate that target, have failed (45), suggesting a need for novel approaches to treating sepsis. Not only do we believe we have identified a novel target capable of regulating multiple aspects of sepsis pathophysiology, but also the timing of intervention. This lends itself to identifying FES as a treatable trait (46), where, depending on the timing of intervention and the levels of FES expression or activity, may result in a different approach to treating a patient’s sepsis (upregulating FES expression or inhibiting FES activity).

